### Comparative Validation Substudy

A validation substudy will be conducted with 19.84% (200/1008) of participants to compare the data collected using the app with a structured multiple-pass 24-hour recall method, which is a well-established and valid method of collecting dietary intake data for population groups [48]. The three daily 24-hour recalls will be conducted in accordance with the methods used in the previous validation study for the eDIA app [35,36]. The researcher will administer the recall using the newly developed automated ASA24-Australia system, which is based on the National Cancer Institute system but uses an Australian database of foods [49]. The quantities of food will be estimated from the Food Model booklet provided. Participants will volunteer to complete the 24-hour recalls in the substudy, and those consenting will be randomly selected to participate by the REDCap system aiming for a representative sample from each subpopulation quota.

The mean or median intakes of energy and all macronutrients will be determined with the addition of specific micronutrients of interest, from the 3 days of 24-hour dietary recalls and EaT app records. Food groups for validation include the core foods (grain foods; fruits; vegetables, and legumes/beans; lean meats and poultry, fish, eggs, tofu, nuts and seeds and legumes/beans; and milk, yogurt, cheese, and alternatives) and discretionary foods and beverages listed in the Australian Dietary Guidelines [46]. As per previous research, differences will be determined using paired *t* tests (normally distributed data) or Wilcoxon signed-rank test (skewed data), and correlation coefficients will be calculated on unadjusted, energy-adjusted, and deattenuated values. Cross-classification and Bland-Altman plots will be used to assess agreement between the EaT app and the 24-hour recalls. For all statistical analyses *P*<.05 will be considered the level of significance, but multiple tests will be appropriately adjusted.

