## Methods

### Aims

The study will determine how frequently young adults purchase and consume foods away from home in the context of their entire diet, and what types of foods they are purchasing and consuming. The relative contributions of different food outlets (eg, fast food chain, independent takeaway food store, coffee shop, restaurant, cafeteria) to overall food and beverage intake of young adults will be established. Finally, the extent to which food and beverages consumed away from home contribute to the total energy and nutrient intake of young adults will be determined using the complete 3-day food and beverage intake data records.

As a substudy, the comparative validity of data collected by the app will be determined using the 24-hour recalls.

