### Screening and Consent

The screening survey (Textbox 1) will be administered at recruitment to collect basic demographic data and consent using the Web-based REDCap research management system [33]. The REDCap system will be programmed to screen participant demographics to fill the study’s demographic quotas. The REDCap system also allows stratified randomization in the substudy (refer to section below).

After completion of the screening questionnaire and enrollment, participants will be notified of their dietary data collection dates, and emailed instructions on how to download and sign up to use the Eat and Track (EaT) app, and obtain a user guide for the EaT app and a copy of the Australian Bureau of Statistics Food Model booklet [34] to assist with estimating portion sizes. Links to useful information on the study website will also be available, including an electronic version of the Food Model booklet.

The study website (Figure 2) was developed to provide information for those participating in this study and future participants. It contains information about the study, its funding and partners, links to the screening questionnaire, technical guides and videos for participants, and links to the Food Model booklet. Potential participants can also contact the study team via email through the website.

Participants will be taught how to use the app using instructional videos and will have access to these videos at all times throughout the study via the study website. Additionally, participants will need to view 3 tutorial screens in the app before they can start recording their intake. They will then record all food and drinks for 3 consecutive days.

Screening questionnaire.Demographics:AgeGenderAboriginality and ethnicityLanguage spoken at homeEducation attainmentPostal code of home addressLiving arrangementRelationship statusEmployment and studyIncomeScreening questions:Do you own a working smartphone?On average, do you have at least one drink, snack or meal you buy away from home each week?(Females only) To your knowledge, are you pregnant and/or breastfeeding?Have you ever been diagnosed or treated for (choose all that apply)?Anorexia Nervosa (screen out)Bulimia Nervosa (screen out)Other eating disorder (screen out)Mental illnessIllicit drug useDiabetesNone of these

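### If the three 24-hour recalls cover the same days as the app record, as the text implies, the planned deattenuated correlations are biased upward

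*Protocol article*

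**What the plan says.** The Aims section sets the purpose of the substudy: "the comparative validity of data collected by the app will be determined using the 24-hour recalls". Its size is given under Comparative Validation Substudy: "A validation substudy will be conducted with 19.84% (200/1008) of participants".

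On timing, that section says: "The three daily 24-hour recalls will be conducted in accordance with the methods used in the previous validation study for the eDIA app". Intakes are then taken "from the 3 days of 24-hour dietary recalls and EaT app records". For the app itself, Screening and Consent says: "They will then record all food and drinks for 3 consecutive days". No section states in so many words that the recalls refer to the app days.

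On analysis, the section plans paired t or Wilcoxon tests. It adds that "correlation coefficients will be calculated on unadjusted, energy-adjusted, and deattenuated values" and that "Cross-classification and Bland-Altman plots will be used to assess agreement between the EaT app and the 24-hour recalls". It gives no deattenuation formula and no source for a variance ratio.

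On portion sizes in the recalls: "The quantities of food will be estimated from the Food Model booklet provided". App users are offered the same booklet for foods they do not weigh.

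**The concern.** Deattenuation is meant to undo the weakening of a correlation that arises when a few reference days stand in for usual intake. In its usual form it multiplies the observed correlation by sqrt(1 + lambda/n), where lambda is the within-person to between-person variance ratio of the reference method and n is the number of reference days. This works when the two methods sample different days, because each method's day-to-day variation is then noise to the other.

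When both methods describe the same days, a heavy-eating day is heavy in both records. That variation adds to the covariance as well as to the variances, so it does not pull the correlation down. Correcting for it adds something that was never lost. The result is a coefficient above anything it could reasonably be meant to estimate. It would also be the highest of the three reported correlations, and so an easy one to quote as evidence of validity for an app that is an updated version of its predecessor.

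**Working it through.** **The plan's own figure.** 200/1008 = 0.1984, which matches the stated 19.84%. The article states no target correlation, precision or variance component for the substudy.

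**Which days.** These points indicate the same 3 days:
- The recalls are described as daily and number three, and the app record runs for 3 consecutive days.
- Population Sampling asks for a commitment to 3 consecutive days only, and no second recording window is described.
- The final questionnaire follows once those 3 days are complete.
- Paired tests and Bland-Altman plots suit records of the same days.

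Against certainty, recall methods are deferred to an earlier study, and the flowchart is not available here.

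**Model (assumed).** On each day, app = T + D + eA and recall = T + D + eR. T is usual intake with variance 1. D is the true day-to-day deviation with variance L. The method errors are independent, each with variance e per day. Each method is averaged over 3 days.

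**Same days.**
- Variance of each 3-day mean: 1 + (L + e)/3.
- Covariance: 1 + L/3.
- Observed r = (1 + L/3) / (1 + (L + e)/3).
- Recall-based ratio: lambda = L + e.
- Deattenuated r = observed r × sqrt(1 + (L + e)/3) = (1 + L/3) / sqrt(1 + (L + e)/3).

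**Two possible targets.**
- App with usual intake: 1 / sqrt(1 + (L + e)/3).
- App with true intake on those days: sqrt(1 + L/3) / sqrt(1 + (L + e)/3).

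Dividing, the deattenuated coefficient is (1 + L/3) times the first target and sqrt(1 + L/3) times the second. The error variance cancels from both ratios, so the coefficient is too high for any L > 0. The excess over the first target is 0.5/3 = 17%, 1/3 = 33% and 2/3 = 67% at L = 0.5, 1 and 2.

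| L | e | Observed r | Deattenuated r | App with usual intake | App with true intake, same days |
|---|---|---|---|---|---|
| 0.5 | 1 | 0.78 | 0.95 | 0.82 | 0.88 |
| 1 | 0.5 | 0.89 | 1.09 | 0.82 | 0.94 |
| 1 | 1 | 0.80 | 1.03 | 0.77 | 0.89 |
| 1 | 2 | 0.67 | 0.94 | 0.71 | 0.82 |
| 2 | 1 | 0.83 | 1.18 | 0.71 | 0.91 |
| 2 | 2 | 0.71 | 1.09 | 0.65 | 0.85 |

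For example, at L = 1 and e = 1, observed r = (4/3)/(5/3) = 0.80, the multiplier is sqrt(5/3) = 1.29, and the product is 1.03.

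**When it passes 1.** Setting (1 + L/3)² > 1 + (L + e)/3 gives L + L²/3 > e. At L = 1 the left side is 1.33, so e = 1 passes and e = 2 does not.

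**Simulation** (200 participants, 1,500 replicates). With the same days, the share of deattenuated coefficients above 1 was 100% at (L, e) = (1, 0.5), 83% at (1, 1), 100% at (2, 1) and 91% at (2, 2). With different days it was 0 to 0.5%.

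**Different days.** The covariance falls to 1. At L = 1 and e = 0.5, observed r = 1/1.5 = 0.67, and the correction gives 0.67 × sqrt(1.5) = 0.82. That equals the usual-intake target, so the correction is valid there.

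**The case against.** The strongest reply is that both premises are inferred. The article never says that the recalls refer to the app days, and it does not give the formula. A condensed article may leave both to a fuller document. Random recall error does attenuate a same-day correlation, so a correction limited to that component would be legitimate. This stands. It makes the point conditional, and it means that deleting the coefficients is not the only remedy.

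It does not remove the point. If the recalls fall on other days, deattenuation is sound, but individual limits of agreement and cross-classification then mix true changes in diet with disagreement between methods. Either way the days must be stated.

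Four stronger readings are tempting, and the documents do not support them:
- *The substudy as a whole will overstate the app's validity.* Only the deattenuated coefficient is biased by this mechanism. The unadjusted and energy-adjusted correlations, paired tests, cross-classification and Bland-Altman analyses are reported beside it.
- *The coefficients will exceed 1.* That depends on variances the article does not give; 0.94 and 0.95 also appear in the table.
- *All main-study estimates rest on this substudy.* The article also cites validation of the predecessor app, and no main analysis is said to use the deattenuated coefficient.
- *The uncorrected correlations are upper bounds.* With independent errors at L = 1 and e = 0.5, the observed 0.89 lies below the app's correlation of 0.94 with true intake on those days. Shared error could push r up, but its size is unknown. App users may also weigh foods or accept a default portion, so the booklet is only partly shared.

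**Conclusion.** The concern holds in conditional form. If the recalls cover the app days, which is the natural reading, and the usual within/between correction is applied, the deattenuated correlations are biased upward for any true day-to-day variation. The direction does not depend on the variances chosen; the size does. The 17% to 67% range rests on L between 0.5 and 2, errors independent between methods, and a variance ratio taken from the recalls. The defect is confined to one of the planned agreement measures. It still warrants correction, because the article positively chooses that measure and the remedy is cheap.

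**What to change.** State in Comparative Validation Substudy which days the recalls cover.

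**If they are the app days:** remove the deattenuated coefficients, or limit the correction to recall error that the app does not share. In the model above, the limited correction multiplies observed r by sqrt((1 + (L + e)/3) / (1 + L/3)). At L = 1 and e = 0.5 this is 0.889 × sqrt(1.5/1.333) = 0.94, the correlation with true intake on those days. Base the statement on validity on the unadjusted and energy-adjusted correlations with 95% CIs and on the Bland-Altman limits. Add that errors common to two self-report methods, such as those from the shared Food Model booklet, may inflate the correlations, without calling them upper bounds.

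**If they are other days:** deattenuation may stay, but describe the Bland-Altman limits and cross-classification as including true day-to-day variation.

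The cost is a sentence or two of text and no new data. The downside is that the reported correlations will look less favourable.

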### Statistical Analysis

#### Mean Intake of Energy and Nutrients

Data collected from the EaT app will be used to determine mean, median, and 95% CI of daily intakes of energy, macronutrients, and micronutrients as well as the contribution of each of the macronutrient to energy content. Misreporting of energy intake will be identified using the Goldberg criteria [50], and sensitivity analysis will be undertaken to assess their inclusion or exclusion from the primary analysis. Energy and nutrient intakes will be compared with Australian Nutrient Reference Values [51] applicable for each age and sex group and the usual intakes from the latest Australian Health Survey [6]. Multivariate regression models will be used to determine the various health, social, and environmental factors associated with consumption of energy and nutrients. To control for multiple comparisons, a significance level of *P*<.01 will be considered for these calculations.

Demographics questionnaire.Anthropometry and diet statusSelf-reported height and weightHow often the participant attempted weight loss in past 12 months, including currentlyWhether the participant is motivated by eating healthy food, losing weight, staying fit and active, or their appearanceDiet and eating behaviorsSelf-perceived healthiness of their dietFood avoidance for health, cultural, or ethical reasons, including vegetarianismSupplement useFrequency and usual timing of meals and snacksFood securityAdequacy of factors influencing diet, including cooking skills, cooking equipment, time available to cook, and access to healthy foods in their local areaQuality and variety of healthy foods in their local areaWho does the cooking in their householdHow often meals and snacks are eaten in front of the televisionAverage weekly amount they spend on eating out of homeReasons for eating out of homeNutrition literacyKnowledge of the Australian Government’s recommended number of serves of the 5 core food groupsHealth behaviorsAlcohol consumption and consumption patternsPhysical activity and sedentary behaviors at work and during leisure timeSleep patterns and durationSelf-perceived health and well-beingTobacco and e-cigarette useDietary monitoringWhether they would be interested in logging single foods with appsWhat aspects of their diet would participants be interested in logging (if any)Eat and Track app usabilityEase of useIf the app is frustrating to useWhether the participant had to make corrections

#### Mean Consumption of Food Groups

Food consumption data from the EaT app will be classified into their respective food groups to determine mean intakes. Food groups for validation include the core foods (grain foods; fruits; vegetables, and legumes/beans; lean meats and poultry, fish, eggs, tofu, nuts and seeds and legumes/beans; and milk, yogurt, cheese, and alternatives) and discretionary foods and beverages listed in the Australian Dietary Guidelines [46]. Mixed dishes will be disaggregated into their individual ingredients to enable accurate classification, using the AUSNUT recipe database [52]. The proportion of participants meeting the intake for recommended daily number of serves for each food group from the Australian Dietary Guidelines [46] will be determined. Multivariate regression models will be used to determine the health, social, and environmental factors associated with consuming the recommended amounts of each food group.

#### Consumption of Foods Purchased and Eaten Away From Home

The average frequency of meals, drinks, and snacks (collectively, and by occasion) purchased and eaten away from home will be calculated. Multivariate regression models will be used to determine the health, social, and environmental factors associated with consumption of foods purchased and eaten away from home. The relative contribution of foods purchased and eaten away from home to total energy and macronutrient intake will be calculated.

### Data Mining

In addition to our usual epidemiological approach, the data will be analyzed using data mining and machine learning techniques employed by information technology scientists. A clustering technique to automatically partition the participant population into groups with similar energy and nutrient intake, and food group consumption patterns will be applied. The resulting clusters of food consumption will be labeled according to their common patterns, for example, high processed meat and takeaway consumption; high fish, fruit, and vegetable consumption. These clusters will then be analyzed for the predominant health, social, and environmental characteristics of each cluster and checked for common associations (such as participants with healthier diets, also exercising regularly, having healthier BMI, not skipping breakfast, and mainly eating at home).

Data mining techniques such as decision trees, neural networks, and support vector machines will be used to build predictive models; for example, to predict the type of diet (high quality or poor quality, assessed by the Healthy Eating Index for Australian adults [53]) based on the frequency and contribution of foods eaten away from home and health, social, and environmental variables. In contrast to standard statistical methods such as multivariable linear regression, these techniques are capable of assessing complex nonlinear relationships and are less sensitive to outliers (data points that correspond to exceptional, nonrepresentative cases). Decision trees offer additional advantage in that they can be represented as a set of if-then rules and are thus easy to explain and use for decision making.

Association rule and time-series mining will be used to find frequent relationships between the variables, for example, what types of foods are typically eaten together at home and away from home by the different groups, whether budget constraints and high stress levels imply fast food consumption regardless of the education level, and whether there are temporal associations.

## Results

Recruitment is underway, and results will be available in 2018.

## Discussion

There is a lack of data on foods purchased and eaten away from home in the context of total dietary intake by young adults in Australia. Our cross-sectional study is designed to determine the frequency and quantity of foods purchased and consumed away from home by young adults in NSW, Australia. The outcome measures will detail the contribution these foods make to young people’s dietary intakes, in terms of energy, nutrients, deleterious nutrients, and food groups and its impact on whether diets are compliant with national recommendations. Population monitoring of consumption of foods prepared and eaten outside the home are most usually by short questions on frequency. This study will provide detailed data about the dietary habits of young people and the sources of their food.

### Smartphone Dietary Assessment

Smartphone dietary assessment has emerged as a promising method for increasing participant acceptability and accuracy of the data collected [35,54] and has been shown to be a valid measure for assessing nutrient and food group intakes in population groups [35,36,55,56]. The database underpinning the EaT app assists participants record foods eaten away from home as the commercial fast food chain products are listed by the portions on offer, and we have provided instructions for recording all other foods with weighing or using the Food Model booklet. The extensive usability testing conducted, provision of aids to assist with estimation, and prompts to weigh foods aim to increase the accuracy of portion size estimations.

Although the EaT app has been developed as a research dietary assessment tool and therefore provides no feedback on nutrients consumed to participants, the app could be adapted as a dietary monitoring tool for individual use. As the majority of the available weight management apps have US databases, or hybrid US and local crowdsourced databases, Australian participants have difficulty recording their foods, leading to inaccuracy [57]. There is a need for an app for accurate dietary self-monitoring.

### Conclusions

This study is the first in Australia to provide detailed information on foods purchased and eaten out of home. By incorporating information from the largest fast food chains in Australia in the app’s food composition database, it is also the first dietary assessment app internationally to have a specific focus on eating out. The requirement of participants to record where they sourced each food or drink will also provide the first estimation of how often young Australians are eating out, and what proportion of their nutritional intake is derived from such meal occasions. This will enable the identification of foods and consumption behaviors of concern that should become the focus of future health promotion efforts for this target audience. Accurate and detailed measurement is important to ensure evidence-based programs.

## Appendix

Multimedia Appendix 1 Sampling Diagram.

## Abbreviations

ARIA+: Accessibility/Remoteness Index of Australia
BMI: body mass index
EaT: Eat and Track
eDIA: electronic Dietary Intake Assessment
IRSAD: Index of Relative Socio-economic Advantage and Disadvantage
NSW: New South Wales
SES: socioeconomic status
